## Study Outcome Measures

### Primary Outcome Measures

- The number of clinical malaria episodes per year of follow-up.

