Ideally, we would like to know the drug level just prior to a detectable parasitemia in the participant since at that level, parasites were able to begin to replicate. Since it is impossible to anticipate when a new patent parasitemia will occur, we will attempt to predict the level retrospectively by obtaining the pharmacokinetic curve in the population. We will also measure the level at the time of recurrent parasitemia in case the participant was found to vary significantly from the mean.

1. Assess the effect of population movements on the risk of malaria infection.

- Risk of malaria in children who traveled outside the city compared to those who did not.

Our interest is the first incident of malaria. Malaria illness will be defined as any level of microscopy-confirmed *Plasmodium falciparum* parasitemia accompanied by signs or symptoms consistent with malaria either leading to treatment-seeking behavior or reported during follow-up visits. This definition is more inclusive since practicing physicians in a malaria endemic area would treat a person who presents complaining of illness and who had documented parasitemia. This definition will enable the longitudinal study to capture all first episodes of malaria illness that would be treated under standard medical practice. Time to malaria illness after baseline is defined as number ofdays without malaria illness after baseline up to the date of the first illness. Dates will be recordedfor all the events occurring prior to or during follow-up.

1. Assess the spatial patterns and the environmental determinants of malaria infection

- Distribution of malaria cases in relation to environmental factors in Ndirande.

In order to evaluate whether there is clustering of cases and/or spatial correlation with environmental variables, we will carefully analyze the spatio-temporal pattern of all cases. All new malaria illnesses after the initial treatment will be escorted home and their location geo-referenced using GPS. Information will be entered into ArcGIS (*ESRI, Redland, CA*) to create a spatial point pattern. This will be linked to the database with information on health, demographic, economic, social, ecological and agricultural characteristics.

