## Definition of treatment outcomes

The 2004 WHO definitions of treatment outcomes will be used as follows:

Therapeutic efficacy will be defined as:

- Early treatment failure (any one of the following)
  - danger signs or severe malaria on days 1, 2 or 3, with parasitemia. Hemoglobin less than 5 without any other signs of severe disease when a participant is receiving therapy will not be a criteria for Early Treatment Failure as hemoglobin levels frequently decrease even with effective therapy.
  - parasitemia on Day 2>Day 0 level
  - axillary temperature > 37.5oC on day 3 in the presence of parasitemia
  - parasitemia on day 3 > 25% of day 0 level
- Late clinical failure
  - development of danger signs, severe malaria or axillary temperature > 37.5oC or a history of fever within the past 24 hours in the presence of parasitemia during days 4-28
  - and no criteria for early treatment failure
- Late parasitologic failure
  - Presence of parasitemia on day 28 without fever
  - and without previously meeting any of the criteria for early treatment or late clinic failure
- Adequate clinical and parasitologic response
  - absence of parasitemia on day 28
  - and without previously meeting any of the criteria of early treatment or late clinical failure

A new episode of malaria will refer to any episode of clinical malaria (symptoms and a positive malaria smear) that occurs more than 14 days after therapy.

If a seizure meets the following criteria of a febrile seizure, the episode will not be considered a danger sign. The following criteria must be met:

1. Occurring in the presence of a reported or documented fever or with a rise in temperature.
2. Generalized seizure witnessed by reliable family member or study staff
3. Duration ≤30 minutes
4. Absence of mental status impairment two hours after the event..
5. Normal neurological examination by a study clinician or investigator within 24 hours of seizure.

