### Reasons for Withdrawal

Participants will be removed from the study if:

- Any clinical adverse event (AE), laboratory abnormality, intercurrent illness or other medical condition occurs such that continued participation in the study would not be in the best interest of the subject
- If the participant requires chronic antimicrobial therapy. For example, children who are found to be infected with HIV will be referred for trimethoprim-sulfamethoxazole prophylaxis and anti-retroviral eligibility evaluation and removed from the study
- Participants who miss ≥ 2 consecutive routine visits will be removed from the study

Participants may withdraw voluntarily from the study at any time.

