## Sample Size Considerations

In a previous longitudinal study of malaria in this population, we found that the mean annual incidence of malaria was approximately 2.5 episodes per year (59) with a standard deviation of approximately 2. Chloroquine is presently highly effective in treating malaria and has a prolonged prophylactic effect, so we have estimated a mean rate of 1.5 malaria episodes per year with chloroquine alone. We derived the sample size required to detect a decrease in the mean to 1.0 episodes per year assuming a Poisson distribution and using a 2 sided test with alpha= .05/3=.0166. The test size was adjusted to accommodate the 3 treatment versus control comparisons. With the above requirements and for a 2 treatment contrast, 120 subjects with complete observation are required per treatment arm to have 90% power (PASS 2005). To account for migration and other causes of attrition, we will enroll an additional 33% (40 subjects) in each regimen. We will accrue 160 per arm for a total of 640 subjects.

Because of the currently estimated efficacy of chloroquine alone in Malawi (in excess of 95%), we are unlikely to determine differences in initial administration (day 28) efficacy between the treatment arms. Power is limited as all arms should have very few early failures. Rates of anemia (<8 mg/dl) at the end of one year should be available in ~120 subjects per arm. The 95% CI half-width for the difference in anemia rates, calculating the variance with a rate of .2, is approximately .10. Thus, the selected sample size should be informative about larger treatment arm differences in anemia rates.

To determine the population pharmacokinetic curve for chloroquine, we have designed a randomized unbalanced study. All participants will have chloroquine levels determined prior to drug administration, at day 14 and at one additional randomly assigned time point. The assignment will be weighted to increase measurement on day two. Planned Interim Analyses

The DSMB will decide when it would like to conduct the interim analysis. The data to be reviewed at this meeting will include safety and efficacy data.

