## Final Analysis Plan

The final analysis of the primary objective will be a comparison of incidence rates of malaria treatment episodes per year of follow-up (not including the first infection occurring at enrollment) in each arm of the study. The rates and 95% confidence intervals will be calculated using Poisson distribution. Reported antimalarial drug use without documented positive malaria smear will not count as a malaria treatment episode. Malaria episodes treated with non-study medicines at Queen Elizabeth Central Hospital with verified positive malaria smears will be counted as malaria treatment episodes, and any such treatments will be compared among groups to rule out bias due to different rates of non-study treatment. Withdrawal of participation is described above and includes participants who miss ≥ 2 consecutive routine follow-up visits. For the primary study endpoint, follow-up time for participants while they are enrolled in the study will be included in the analysis. For participants who were withdrawn after missing > 2 consecutive follow-up visits, time after the last visit will be censored from incidence analysis.

Drug efficacy for the first and subsequent episodes of malaria will be compared using Kaplan-Meier 28-day survival estimated and compared using Cox proportional hazards regression. Per-protocol analysis will be used to compare treatment efficacy, with data excluded from treatment episodes for which treatment outcome cannot be determined. Survival analysis will also be used to assess time to first resistant infection in each arm. Categorical data including episodes of liver, kidney or neurological toxicity and presence of anemia will be compared using 2 analysis. Logistic regression will be used to adjust for covariates.

Survival analysis will be used to assess the role of travel outside of Blantyre and bed net use on the risk for malarial and time to first malaria episode. This analysis will be conducted both with and without the inclusion of treatment arm as a covariate in the analysis.

Data will be entered in to the database on the computers at the field site. On a daily basis, the data will be transferred via the internet to the EMMES corporation web-based system.

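### Section 11.3 censors unobserved time only after more than two missed visits, although withdrawal occurs at two, so some unobserved weeks stay in the primary rate

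*Protocol*

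**What the plan says.** **Missed visits.** Section 5.4.3 states: "Participants who miss ≥ 2 consecutive routine visits will be removed from the study". Section 11.3 refers back to withdrawal with the same threshold of two or more. It then sets the general rule for the denominator: "For the primary study endpoint, follow-up time for participants while they are enrolled in the study will be included in the analysis". The exception follows: "For participants who were withdrawn after missing > 2 consecutive follow-up visits, time after the last visit will be censored from incidence analysis".

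**Episodes.** The primary outcome (3.2.1) is "The number of clinical malaria episodes per year of follow-up". Section 4.3 defines a new episode as clinical malaria "that occurs more than 14 days after therapy". Section 7.3.1 codes a symptomatic recurrence within 14 days of starting study treatment as a treatment failure, to be given rescue therapy. Section 11.3 adds a rule for the hospital: "Malaria episodes treated with non-study medicines at Queen Elizabeth Central Hospital with verified positive malaria smears will be counted as malaria treatment episodes". It gives no time limit there.

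**Time to first illness.** For the travel objective, section 3.2.2 counts days "without malaria illness after baseline up to the date of the first illness". Illness there means any smear-confirmed parasitaemia with signs or symptoms, and no minimum gap from enrolment is stated.

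**The concern.** The two thresholds in section 11.3 cannot both describe the same children. Removal occurs at the second miss, so if it is prompt, few or no children ever reach a third miss while enrolled. Read literally, the censoring sentence then reaches almost nobody. The child it should cover, one removed at exactly two misses, comes under the general rule, and the weeks between the last attended visit and removal are counted as follow-up. Those weeks add person-time in which routine surveillance was absent and few episodes could be recorded. The rate is understated, and if such withdrawals differ by arm the rate ratio shifts as well.

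The numerator and denominator also leave smaller questions open. The 14 days after each treatment cannot hold a new episode but stay in follow-up time. It is not stated whether a recurrence within 14 days counts when it is treated at the hospital. The time-to-first-illness definition could take in the enrolment infection itself.

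**Working it through.** **Planned figures (11.2).** The control rate is given as: "we have estimated a mean rate of 1.5 malaria episodes per year with chloroquine alone". The combination rate is 1.0, so the planned rate ratio (RR) is 1.0/1.5 = 0.667. The two-sided alpha is 0.05/3 and power is 90%. The Poisson-regression formula with a binary covariate (Signorini) gives a total N = [2.394 × √4 + 1.282 × √(2 + 2/0.667)]² / (1.5 × (ln 0.667)²) = 237.5, or 118.8 per arm. The protocol's 120 reproduces, with 90.3% power at 120. Attrition: 120/(1 − 0.25) = 160. The sample size is not in question.

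**Missed visits.** Routine visits are every four weeks (7.3), so two misses span 2 × 28 = 56 days. The base is one full year per child. The share of children withdrawn at exactly two misses is not in the protocol, so a range is assumed. The top of the range, 25%, equals the whole attrition allowance (40 of 160).

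- 5%: 0.05 × 56/365.25 = 0.8% of person-time
- 10%: 1.5%
- 25%: 3.8%

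Effect on the ratio: RR = 0.667 × (1 + s₁ × 56/365.25) / (1 + s₂ × 56/365.25), where s₁ is the share on chloroquine alone and s₂ the share on the combination.

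| s₁ | s₂ | RR |
|---|---|---|
| 10% | 10% | 0.667 |
| 5% | 20% | 0.667 × 1.0077/1.0307 = 0.652 |
| 0% | 25% | 0.642 |
| 20% | 5% | 0.667 × 1.0307/1.0077 = 0.682 |

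The shift can go either way.

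**The 14-day window.** Blocked days per child-year, enrolment treatment included: 14 × (1 + 1.5) = 35 (9.6%) on chloroquine and 14 × (1 + 1.0) = 28 (7.7%) on a combination. If the planned rates are per calendar year, the ratio per day at risk is (1.0/337.25)/(1.5/330.25) = 0.653. If they are instead per time at risk, the protocol's rate is L(1 − d)/(1 + Ld), with L the rate and d = 14/365.25. That gives 1.36 and 0.93, a ratio of 0.679 against 0.667. In this second case, power at 120 per arm is 84.1% with calendar time and 87.3% with time at risk.

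**Recurrences by day 14.** In the 2005 trial (Background, Table 1) chloroquine had 1 failure among 80 known outcomes, 1.25%. Treatments per child-year are 2.5 on chloroquine and 2.0 on a combination. The ratio with early recurrences counted is (1.0 + 2.0 f₂)/(1.5 + 2.5 f₁), where f₁ and f₂ are the assumed proportions failing by day 14:

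- 1.25% in both arms: 1.025/1.531 = 0.669
- 10% in both arms: 1.2/1.75 = 0.686
- 5% on chloroquine, 1.25% on the combination: 1.025/1.625 = 0.631

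**The case against.** The threshold of two or more is stated twice, so the strict inequality looks like a slip of one character, and an analyst might censor correctly anyway. That is a fair account of its origin. It does not settle what the text requires, because the general rule picks up the children whom the exception leaves out. It is also fair that the protocol expects losses from migration and voluntary withdrawal, so 25% is a ceiling. A child who misses routine visits may still attend unscheduled ones, so 56 days is an upper figure for each child.

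On the 14 days, the protocol defines the outcome per year of follow-up and presents incidence as a measure of disease burden and use of health resources. Calendar time suits that purpose. Fourteen days is not a clean limit of risk either, since the pharmacokinetics table gives chloroquine activity for up to 70 days. This stands: the primary denominator is not an error, and time at risk belongs in a sensitivity analysis.

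On hospital cases, a reader might infer that an early recurrence counts if treated at the hospital and not if rescued at the clinic. The protocol does not say so. Section 7.3.1 codes recurrences within 14 days as failures without reference to place, and the hospital sentence in 11.3 does not claim to override it. The text is silent on the overlap, which does arise because sections 6.7 and 8.2 send severe cases to the hospital.

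A reader might also infer that these rules pull the ratio toward 1, or credit an arm whose treatment fails early. The documents do not support that in general. Counting early recurrences gives 0.669 at the earlier trial's failure rate in both arms and 0.686 at 10% in both, so leaving them out puts the ratio further from 1. The opposite holds only if failure is more frequent on chloroquine alone. Treatment failures are also compared as a secondary outcome, and a day-28 response of 75% or less prompts discussion by the data and safety monitoring board.

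**Conclusion.** The contradiction on missed visits holds. It lies within section 11.3 and between 11.3 and 5.4.3, and it affects the person-time of the primary endpoint. Its likely size is modest: about 0.8% to 3.8% of person-time under an assumed 5% to 25% of children, no change in the ratio when shares are equal, and 0.652 instead of 0.667 at 5% against 20%.

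The other points are secondary. The 14-day effect is about 2% of the ratio and conservative at the planned rates. The hospital rule is an omission that is negligible at the failure rate seen in 2005, and it matters only if early failure becomes frequent or differs between arms. The time-to-first-illness gap concerns the travel analysis alone.

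**What to change.** - In 11.3, change the censoring threshold from more than two to two or more consecutive missed visits, and censor at the last attended visit.
- Add a sensitivity analysis of the primary rate that removes the 14 days from each treatment start, enrolment included, from time at risk.
- Reconcile the hospital sentence in 11.3 with 4.3 and 7.3.1, so that a recurrence within 14 days enters the count the same way wherever it is treated. Applying the 14-day rule at the hospital would by itself take severe early recurrences out of the primary count. For that reason, add a supportive analysis that counts all smear-confirmed malaria illnesses, recurrences by day 14 included, over full follow-up.
- In 3.2.2, state that the enrolment infection does not count as the first illness.

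The cost is wording and programming. Visits, treatments and smears are already recorded under the protocol, and no visit, treatment or withdrawal rule needs to change.

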# Background Information and Scientific Rationale

## Background Information

In 1993, Malawi was the first sub-Saharan African country to discontinue the routine use of chloroquine and to elevate the antifolate combination sulfadoxine-pyrimethamine (SP) to the antimalarial of first choice nationwide. The decision was based on chloroquine's increasing failure to produce adequate clinical and hematological recovery (1). Since 1993 SP has been the only available treatment for uncomplicated malaria in all government health facilities, and is dispensed without prescription. Although chloroquine has remained available by prescription and through unauthorized private sources, a national information campaign was largely successful in convincing health practitioners and the public to accept SP as the treatment of choice for children with malaria.

It has been speculated that years of reliance on antimalarials other than chloroquine might lead to the reemergence of chloroquine-sensitive *P. falciparum* and permit the reintroduction of this safe and affordable drug. We retrospectively measured the prevalence of the *pfcrt* 76T molecular marker for chloroquine-resistant *P. falciparum* malaria in Blantyre, Malawi. From 1992 to 2000, we documented a gradual decrease in prevalence of the mutation associated with chloroquine resistance (2) and neither we nor other investigators have found any parasites with the mutation since 2001 ([name], personal communication and [name], personal communication).

We have demonstrated the clinical efficacy of chloroquine, as well. In preparation for the present study, we conducted a trial to assess the efficacy of chloroquine in treating children with uncomplicated malaria at the Blantyre Malaria Project Research Clinic at the Ndirande Health Centre from May through December, 2005. Two hundred ten children with uncomplicated malaria were randomly assigned to receive either SP, the standard therapy in Malawi, or chloroquine. Among 105 children randomized to receive chloroquine monotherapy, only one experienced treatment failure. The results are shown in Table 1. Based on these results, we have determined that chloroquine is safe to use to treat malaria in this population.

|  | Chloroquine | SP |
| --- | --- | --- |
| Adequate clinical and parasitologic response (% per-protocol) | 79 (99) | 16 (18) |
| Early treatment failure (% per-protocol) | 1 (1) | 21 (24) |

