| Late clinical or parasitologic failure (% per-protocol) | 0 (0) | 50 (57) |
| Outcomes unknown | 25 | 18 |
| Total | 105 | 105 |

Table 1: Outcomes of 28-day efficacy study of chloroquine vs. SP for the treatment of uncomplicated malaria among children in Blantyre, Malawi.

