### Efficacy

Chloroquine was the first drug deployed in an attempt to rid the world of malaria after World War Two. It was highly effective initially, but chloroquine resistance emerged in Asia and South America and reached the African continent in the 1970s (15). As we described above, we have documented in Malawi the replacement of predominantly chloroquine resistant parasites in the 1990s by exclusively chloroquine susceptible parasites since 2000, presumed to be a result of the cessation of chloroquine use. The clinical study conducted in 2005 confirmed chloroquine efficacy in the study population.

Because chloroquine currently has a 99% cure rate in Malawi, all study treatments administered in this trial are expected to have very high initial clinical efficacy. Differences between treatment outcomes may be detectable in late recrudescence rates and/or the incidence of malaria episodes over time and other longitudinal measures of efficacy.

Artesunate is the most widely studied antimalarial compound in the literature (16). In a review of 27 randomized controlled studies of artemisinin-based combination therapy (ACT) in comparison with standard therapy, the ACT decreased treatment failure, recrudescence rate and gametocyte carriage (17). The World Health Organization recommends that all countries with endemic malaria adopt ACTs as first line antimalarial therapy (18).

Azithromycin has been used successfully as chemoprophylaxis among semi-immune adults (19;20), but has not displayed adequate efficacy when used as monotherapy. In a small, multicenter trial in India, the combination of chloroquine and azithromycin led to a 28 day parasitologic cure rate of 97%, while the rate for chloroquine alone was only 27% (21). It has also been administered successfully as a malaria prophylactic agent with efficacy of 72% in Indonesia and 83% (when administered daily) in Kenya (19;20).

The combination of atovaquone with proguanil leads to synergistic activity against even multidrug resistant parasites(22). Previous studies have administered AP, without any additional drug, for the treatment of uncomplicated malaria. The efficacy of AP among children was 100% in Thailand for children 5-12 years of age (23) and 94% in Kenya for children 3-12 years of age after 28 days of follow-up(24). In a study in Gabon, among children weighing 5-10 kg, AP had 95% efficacy at 28 days(25).

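### Cox regression is the named comparison of first-treatment 28-day efficacy, but at the protocol's own 1–1.25% failure rate at least one arm may well have no failures, leaving some hazard ratios without a finite estimate

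*Protocol*

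**What the plan says.** Section 11.3 (Final Analysis Plan) states that drug efficacy for first and subsequent episodes will be "compared using Kaplan-Meier 28-day survival estimated and compared using Cox proportional hazards regression". The analysis set is restricted: "Per-protocol analysis will be used to compare treatment efficacy, with data excluded from treatment episodes for which treatment outcome cannot be determined". No other between-arm method is named for this outcome.

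The expected number of failures can be read from three places:

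- Background Information, on the 2005 trial: "Among 105 children randomized to receive chloroquine monotherapy, only one experienced treatment failure". Table 1 of that section puts 25 of those 105 children under unknown outcome, so the evaluable denominator is 80. The one failure was early; there were no late failures.
- The Efficacy subsection of the background expects very high initial efficacy in every arm and gives the reason: "Because chloroquine currently has a 99% cure rate in Malawi".
- Section 11.2 (Sample Size Considerations) puts chloroquine efficacy above 95%, says day-28 differences at first administration are unlikely to be found, and adds: "Power is limited as all arms should have very few early failures". Section 11.2.2 (Efficacy Review) repeats the figure of above 95%.

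Section 3.2.2 defines the first-treatment outcome as the rate of adequate response at 28 days, which is a proportion.

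**The concern.** A Cox hazard ratio needs at least one event in each of the two arms that it compares. If one arm has none, the partial likelihood keeps increasing as the log hazard ratio moves to minus or plus infinity. The software then prints a very large coefficient with a very large standard error, and the Wald interval carries no information. Low power is a different matter: it gives a wide interval around an estimate that exists.

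The protocol foresees very few failures, yet names an event-driven contrast and no alternative. At stake is the planned effect estimate and interval for the first secondary objective. The primary endpoint, annual incidence of malaria episodes, is untouched.

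**Working it through.** **Inputs**

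- Failure rate p: 1% (the 99% cure rate) and 1/80 = 1.25% (Table 1). For sensitivity, 2%, and 5% as the bound implied by efficacy above 95%.
- Children per arm n: 160 enrolled (Section 11.2). Because episodes with undetermined outcome are excluded, a second value applies the 2005 evaluability: 160 × 80/105 = 121.9, about 122. This is an assumption.
- The same p in all four arms, and independent arms.

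**The plan's own figure.** 105 − 25 = 80 evaluable; 79/80 = 98.75% and 1/80 = 1.25%, which the table prints as 99 and 1. The protocol states no expected event count or power for the 28-day Cox comparison, so there is nothing further to reproduce.

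**Formulas**

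- Chance of no failure in one arm: q = (1 − p)^n.
- Chance that at least one of four arms is empty: 1 − (1 − q)^4.
- Chance that a given combination-versus-chloroquine hazard ratio is not finite: 1 − (1 − q)^2.

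| p | n | Expected failures per arm | q | At least one empty arm | A given hazard ratio not finite |
| --- | --- | --- | --- | --- | --- |
| 1% | 160 | 1.6 | 20.0% | 59.1% | 36.0% |
| 1% | 122 | 1.22 | 29.3% | 75.1% | 50.1% |
| 1.25% | 160 | 2.0 | 13.4% | 43.7% | 24.9% |
| 1.25% | 122 | 1.53 | 21.6% | 62.1% | 38.5% |
| 2% | 160 | 3.2 | 4.0% | 14.9% | 7.7% |
| 2% | 122 | 2.44 | 8.5% | 29.9% | 16.3% |
| 5% | 160 | 8.0 | 0.03% | 0.1% | 0.05% |
| 5% | 122 | 6.1 | 0.2% | 0.8% | 0.4% |

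**If the combinations do better.** With chloroquine at 1% and each combination at 0.5% (an assumption), at least one arm is empty with probability 86.6% at n = 160 and 93.2% at n = 122.

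**Losing all three contrasts.** A single empty arm does this only if it is chloroquine: q = 13–29% at 1–1.25%. The other route is three empty combination arms with chloroquine not empty, q³(1 − q). At p = 1% and n = 122 this is 0.293³ × 0.707 = 1.8%. With both routes the range is 14–31%.

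**Check by fitting.** A Cox model was fitted to constructed data with 160 children per arm.

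- Failures 1 (chloroquine), 0, 2 and 3: the empty arm had log hazard ratio −16.0 with standard error about 3,044. The other two were finite, 0.69 (standard error 1.22) and 1.10 (standard error 1.15).
- Failures 0 (chloroquine), 1, 2 and 1: all three log hazard ratios were about 17 to 18, with standard errors of about 5,187.

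The finite case shows what low power alone looks like: exp(0.69) = 2.0, with 95% interval exp(0.69 ± 1.96 × 1.22), about 0.18 to 22. That is very wide, but it can be reported.

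**What an exact interval would give.** The two-sided 95% exact upper limit for the failure proportion is 3.0% for 0/122, 4.5% for 1/122 and 5.8% for 2/122.

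**The case against.** The strongest reply is that Cox regression is a standard choice for a secondary outcome, that a sparse-event fallback is commonly left to the SAP, and that the protocol already admits that the day-28 comparison will be uninformative. No decision rests on it. This carries weight and is why the point is minor. It does not remove it. The comparison method is one that the protocol itself names, and the admission concerns power; it does not say that an estimate may not exist.

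The second reply is that the probability depends on the chosen inputs. This stands. The exact 95% interval for 1/80 runs from 0.03% to 6.8%. The 2005 trial ran from May to December, whereas Section 4.1 puts the transmission peak in December to March. The failure definitions in Section 4.3 count any qualifying parasitaemia, so the 1% may not carry over. The figure of 122 borrows another trial's loss. At 2% failure the problem is uncommon to moderate, and at 5% it disappears. Above 95% is, however, a lower bound on efficacy; 99% is the only point value that the protocol gives.

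A reader might infer more than the documents support:

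- *That the hazard ratios as a set cannot be estimated.* Contrasts between arms that have failures stay finite. At 1% failure, all three are finite in 25–41% of trials (n = 122 to 160).
- *That the first secondary objective would have no result.* Its outcome is a per-arm rate, which is always available, as are the Kaplan-Meier curves. The log-rank test also works unless all four arms are empty (0.2–0.7% at n = 122 and 1–1.25%).
- *That the trial will show failure below about 3% in every arm.* That limit holds only for an arm with no failures at n = 122. At 1–1.25%, at least one arm has three or more failures with probability 41–58%.
- *That the same holds for subsequent episodes or for time to first resistant infection.* The calculation covers first treatment only, and for resistant infection Section 11.3 names only survival analysis, not Cox regression.

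**Conclusion.** The point holds as a minor one on a secondary endpoint. At the failure rate that the protocol's own data suggest, there is a 44–59% chance with 160 evaluable per arm, or 62–75% with about 122, that at least one first-treatment arm has no failure. At least one planned hazard ratio then has no finite estimate or Wald interval. Any given contrast is lost in about 25–50% of trials.

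These figures rest on equal failure rates of 1–1.25%, on independent arms and, for the higher range, on the 2005 evaluability of 80/105. Better-performing combinations raise them; higher failure rates lower them steeply.

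**What to change.** In Section 11.3, for 28-day efficacy at first treatment:

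- Make the main comparison the day-28 failure proportion in each arm with an exact interval. Add the difference of each combination from chloroquine with a score or exact interval, and an exact test. This matches the outcome as Section 3.2.2 defines it and gives a result even when an arm has no failure.
- Keep Kaplan-Meier curves as description. In an arm without failures the usual Greenwood interval collapses to 100%–100%, so intervals should come from the exact method.
- If a hazard ratio is wanted, use Firth-penalised Cox regression with profile-likelihood intervals.

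The cost is analysis wording only. Sample size, visits and data collection do not change. The modest power that Section 11.2 already concedes will remain; the change secures a reportable estimate and interval, not a more sensitive comparison.
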